### Phase 1: designing the intervention

The intervention will be informed by the extant literature regarding the pragmatics and focus for the couple work. It will consist of six sessions [34,35] conducted every two to three weeks [28,47] by registered practitioners at a local voluntary sector counselling organisation. The intervention will be delivered off-site in central Edinburgh, away from the pressures of a busy outpatient hospital clinic where there is usually limited time to discuss psychosexual concerns during healthcare consultations [24].

The content of the intervention will comprise assistance with emotional disclosure [33,48], psycho-education [19,29], relational and sexual needs [29-31] and dyadic adjustment and coping [49,50]. A treatment manual will be developed to guide delivery of the intervention [51]. The manual will comprise information about prostate cancer and its effects, principles of therapeutic change, guidance on using the manual and a detailed session structure plan. This manual-based family-relational-psychosexual support will be based on systemic principles [52-55] combined with techniques from sex therapy, that is, sensate focus [56]. Therefore, the manual aims to integrate components of systemic theory with elements of sex therapy to support intimacy and emotional aspects of the couple relationship.

Specialist training in delivery of the intervention will be provided to practitioners holding accredited counselling or psychotherapy qualifications. Training will include sessions led by men affected by prostate cancer and a systemic practitioner in cancer care. Fidelity to the manual will be assessed as an ongoing process, recorded by practitioner self-report using a checklist provided by the research team.

In line with routine counselling interventions, this study adopts a waiting-list control design [57]. The control group will be offered the intervention if the analysis indicates a significant benefit in quality of life for couples who receive the support.

The session structure for the intervention will cover six main topic areas as follows:

**Session 1 - Getting to know the couple: orientation and engagement.** This first session will outline the support on offer. Topics for discussion will include:

● the couple’s definition of current issues, concerns and problems

● the cancer diagnosis and treatment(s)

● the partner’s role in the context of diagnosis and treatment

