● mapping the support network and wider family system

**Session 2 - The couple’s communication style and relationship.** This session is primarily focused on understanding the patient and their partner as a couple, to explore how they convey love, support, understanding, companionship and affection.

**Session 3- Intergenerational patterns of illness, coping and affection.** Focusing on intergenerational patterns, discussion will centre on the role and meaning of illness in the couple relationship in the context of:

● family resilience

● dyadic adjustment in ill-health

● the role of partners and family when someone is ill

● how people in the family express intimacy

**Session 4 - Couple intimacy before and after cancer.** Intimacy before and after cancer will be explored. A psycho-educational approach will be used to promote closeness and express intimacy after treatment. The place of medical treatments will be considered and techniques from sex therapy will be applied if appropriate for the couple.

**Session 5 - Further exploration of emerging areas.** This session will focus on areas that have emerged in previous sessions where the practitioner and couple wish to give more time to them. This may include more work on increasing levels of intimacy, and improving satisfaction with sexual activity, with discussion of successes or challenges therein.

**Session 6 - Summarising the couple’s accomplishments and future planning.** The final session will summarise work to date, with discussion of relapse prevention and how to take forward progress that has been made, including the setting of short- and long-term goals. This will include a specific focus on maintaining intimacy and dyadic adjustment.

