### Phase 2: determining the parameters for a definitive trial

#### Patient recruitment

Eligible patients will be identified from the urology surgical lists at the Western General Hospital, Edinburgh, UK. The research nurse at the site will apply eligibility criteria before patients are invited to complete the EPIC questionnaire. Patients will be invited to complete the questionnaire via two routes: either on-site at their post-operative follow-up appointment at the outpatient surgical urology follow-up clinic; or by postal invitation from the clinical team.

The recruiting site will complete logs to report recruitment rates at baseline and any attrition following randomisation. Additionally, attendance at the couple support sessions will be logged to assess attrition rates at each stage of the intervention. The recruitment rate for a larger definitive trial will be calculated from the time taken for 68 couples to complete the study.

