#### Data collection

As this is a feasibility study, it is not formally testing hypotheses. Nevertheless, we will examine outcome measures pre/post/follow-up (baseline, end of intervention and six-month follow-up) to evaluate the indicative effect of the intervention on both individual and couple/relational issues. Outcome measures have been selected to prevent over-burdening participants (by capping the length and number of measures used). We have generously estimated that all measures may take 30 minutes to complete, but feel that many participants will complete them in 10 minutes. Validated measures, detailed below, will be used alongside a specially designed *pro forma* for collating additional information on health-service use and demographic data.

In order to assess the feasibility and acceptability of the intervention, practitioners will complete adherence checklists, indicating for each couple which components of the intervention were covered in the therapy.

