#### Statistical analysis

Although hypothesis testing should proceed cautiously in a feasibility/acceptability study, we anticipate that couples in the intervention group will show increased scores for sexual functioning (measured using EPIC) and functional couple relationship (SCORE 15 measure), and decreased scores for anxiety and depression (HADS measure).

The study will therefore estimate the efficacy of this intervention based on the mean difference in primary (EPIC) and secondary outcome measures (SCORE 15, HADS) between the intervention and control groups pre- and post-test. Baseline demographic characteristics will be reported as mean and standard deviation for continuous data and number (percentage) for categorical data. ANOVA will be used to test the within-between group interaction in this two-group design, with two points of measurement (end of intervention and six-month follow-up). Data will be managed and analysed using SPSS version 19 (IBM Corp, Armonk, NY, USA). The significance level applied to all analyses (and any adjustments for *post hoc* analyses) will be set at 0.05.

Analysis of the practitioner adherence checklist data will proceed using frequency counts to identify those areas addressed most frequently. This data will be interpreted with reference to the qualitative appraisal of feasibility and acceptability.

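### The checklist named as the fidelity measure is to be analysed by ranking the topics covered most often, which does not show how much of the manual was delivered to couples who attended

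*Protocol article*

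**What the plan says.** Four places in the protocol article bear on this.

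- **Purpose** (Phase 1: designing the intervention): "Fidelity to the manual will be assessed as an ongoing process, recorded by practitioner self-report using a checklist provided by the research team". No other fidelity measure is named.
- **Form of the data** (Data collection): "practitioners will complete adherence checklists, indicating for each couple which components of the intervention were covered in the therapy". The record is therefore by couple and by component. That sentence gives the purpose as assessing feasibility and acceptability, which the Aims section makes the primary aim.
- **Analysis** (Statistical analysis): "Analysis of the practitioner adherence checklist data will proceed using frequency counts to identify those areas addressed most frequently". The next sentence adds: "This data will be interpreted with reference to the qualitative appraisal of feasibility and acceptability".
- **Attendance** (Patient recruitment): "attendance at the couple support sessions will be logged to assess attrition rates at each stage of the intervention". The checklist analysis does not refer to this log.

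On content, Phase 1 states "The session structure for the intervention will cover six main topic areas as follows" and lists one topic area for each of sessions 1 to 6. Some content is left open by design. In session 4, "techniques from sex therapy will be applied if appropriate for the couple", and session 5 takes up whatever has emerged earlier.

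**The concern.** Fidelity asks whether the manual's components were delivered to the couples who came. The stated analysis asks which topics came up most. These are different questions, and the second does not answer the first.

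Two things are lost. The first is level: a rank order is the same whether nearly everything or less than half was delivered. The second is the cause of a low count. A topic may be counted rarely because couples had left, because the content was conditional and judged unsuitable for that couple, or because the practitioner did not cover it. Only the last is a departure from the manual.

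This matters because the pilot is meant to establish whether a manualised intervention is feasible and to set parameters for a definitive trial. Low attendance and low delivery call for different changes to that trial.

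**Working it through.** The article gives no figure for fidelity, adherence or session attrition, so there is none to reproduce. What follows illustrates how the stated measure behaves.

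**Inputs**

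- Couples recruited: 88 (Sample size calculation; 68 × 1.3 = 88.4).
- Allocation 1:1 (Randomisation, allocation concealment and blinding), so 88 / 2 = 44 intervention couples. The Abstract speaks of 68 couples being randomised; on that reading the arm has 34 and every count below scales by 34/44.
- Six sessions, one main topic area each (Phase 1).
- Cumulative loss of couples by session 6, L: not given. Assumed range 0% to 40%, at a constant rate per session. The value 22.7% is (88 − 68) / 88. It is the article's allowance for loss from the whole study in both arms, not a session attrition rate, and serves only as one point in the range.
- Each topic is assumed to be covered in its planned session and nowhere else.

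**Step 1: the ranking ignores level.** Suppose no couple leaves and delivery across topics 1 to 6 is 100%, 98%, 95%, 90%, 85%, 80%. The counts out of 44 are 44.0, 43.1, 41.8, 39.6, 37.4, 35.2. Multiply delivery by 0.4, so that it runs from 40% to 32%, and the counts are 17.6, 17.2, 16.7, 15.8, 15.0, 14.1. The order is identical. This step needs no attrition.

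**Step 2: raw counts fall with attrition under perfect delivery.** The expected count for the topic of session k is 44 × (1 − L)^((k − 1)/5).

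| Assumed L | S1 | S2 | S3 | S4 | S5 | S6 |
|---|---|---|---|---|---|---|
| 0% | 44.0 | 44.0 | 44.0 | 44.0 | 44.0 | 44.0 |
| 10% | 44.0 | 43.1 | 42.2 | 41.3 | 40.4 | 39.6 |
| 22.7% | 44.0 | 41.8 | 39.7 | 37.7 | 35.8 | 34.0 |
| 30% | 44.0 | 41.0 | 38.1 | 35.5 | 33.1 | 30.8 |
| 40% | 44.0 | 39.7 | 35.9 | 32.4 | 29.2 | 26.4 |

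**Step 3: one count, two explanations.** A session 6 count of 30.8 arises from 30% loss with full delivery (44 × 0.70 × 1.00) and equally from no loss with 70% delivery (44 × 1.00 × 0.70). The count alone cannot tell them apart.

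**Step 4: with a denominator the ambiguity goes.** Dividing by couples attending gives 30.8 / 30.8 = 100% in the first case and 30.8 / 44 = 70% in the second. Under perfect delivery, every topic shows 100% at any value of L.

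**The case against.** The strongest reply is that the data are sound. The checklist is kept for each couple and component, and attendance is logged by stage, so numerator and denominator both exist. That is right. A reader might infer that the trial cannot show whether the manual was delivered; this is true of the ranking as worded, but not of the data to be collected.

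Second, frequency counts need not exclude percentages or per-couple summaries, and an article may leave such detail to a fuller plan. This stands in part: a missing denominator would not by itself be a finding. But the article does state what the counts are for, and that target is not fidelity.

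Third, the counts are to be read with the qualitative appraisal, which includes interviews with practitioners about the content and process of delivery. Interviews can help to explain a pattern. They supply neither a denominator nor a level of delivery. Participants are invited to interview when they complete post-intervention measures, so couples who left and did not return these are not reached by that route.

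Fourth, checklist areas may not map one-to-one onto sessions. Intimacy appears in the plans for sessions 3, 4, 5 and 6. This stands: a reader might infer that the psychosexual content would rank low through attrition, but the article does not support that prediction.

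Fifth, the checklist form is not shown, so it cannot be said to lack a way of marking conditional content as not appropriate. This also stands.

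**Conclusion.** The point holds in a narrow form. The article names a checklist as its fidelity measure and then fixes an analysis that ranks content. The ranking does not show the level of delivery, whatever the attrition. That part rests only on the wording, and on the natural reading that the fidelity checklist and the adherence checklist are the same form.

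The second part, that raw counts for later topics mix attendance with non-delivery, is conditional. It requires couples to leave between sessions and topics to stay in their planned sessions. Its size is unknown: over the assumed range of 0% to 40% loss, the session 6 count under perfect delivery runs from 44 down to 26.4, and at 0% there is no effect. The fall to 34.0 should not be read as the plan's own expectation, because 22.7% is a study-wide allowance for follow-up and couples lost after session 6 would lower no count.

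This is a minor point. The primary outcome, its analysis and the sample size are unaffected.

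**What to change.** Replace the checklist sentence in Statistical analysis with one that uses the per-couple checklist and the attendance log together to report:

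- (a) for each component, the number of couples in whom it was covered divided by the number who attended the session to which the manual assigns it (or at least one such session, where it belongs to several), with conditional components shown separately from core ones;
- (b) for each couple, the percentage of core components delivered, summarised by median and range. Taking the core components of the sessions that couple attended as denominator keeps this separate from attendance;
- (c) session attendance as its own result.

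The link to the qualitative appraisal can stay, and counts of the commonest topics can be kept as description.

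The cost is a little more analysis, a list of which components are core, and, if the form lacks it, one not-appropriate option. No new data source is needed.

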### Phase 3: qualitative assessment of acceptability and feasibility

In addition to the calculation of recruitment and retention rates, a qualitative approach will be used in the post-trial evaluation to assess the acceptability of the intervention. Interviews will be digitally recorded, transcribed and managed using NVivo (version 10) software (QSR International, Doncaster, Australia). The analysis of transcripts will begin with thematic analysis, and subsequently draw on systemic theory, to provide an in-depth understanding of the acceptability of the intervention. This is critical in gaining experiential accounts of psychosexual and relational needs at follow-up to evidence subjective outcomes.

#### Patient and partner interviews

Individual face-to-face interviews will be conducted with participants of the intervention group (N = 10 patients and their partners) and control group (N = 10 patients and their partners). Sampling will be purposive, with interviewees stratified for degree of change, to determine qualitative appraisals of either usual care or the intervention and its success or otherwise. Separate interviews will be used to enable the exploration of private accounts of the experience. Participants will be invited to opt in to an interview when completing their post-intervention measures. The timing reflects the desire to gain feedback on the intervention when recall is likely to be strongest.

Participants in the intervention group will be asked about what was most and least helpful about the couple support, the location and timing of this support, their relationship and use of services, and whether anything could be changed or added to the intervention. Participants in the control group will be asked about their routine care, any support they received in relation to their quality of life, sexual functioning, relationship and use of services.

#### Healthcare professional interviews

Post-intervention interviews will be conducted with key-informant healthcare professionals (N = 10), including those who have had experience of delivering the intervention. Interviews will elicit views on the acceptability and feasibility of the content and process of delivery of the intervention; for example, eligibility criteria, method and timing of recruitment, session structure, timing and duration of intervention. The suitability of the intervention within the context of everyday care packages and current prostate cancer provision in this locale will be assessed, to consider questions such as whether the intervention works better because it is off-site and away from clinical pressures. Determining the acceptability and feasibility of this single-site study will act as a starting point from which the parameters of a definitive trial can be determined.

### Establishing long-term cost implications

Economic analysis will focus on additional costs, compared to usual care, and potential cost savings, using simple modelling to evaluate the affordability of the intervention [63]. Data will be collected from the organisation providing the intervention to provide estimates on (i) duration of appointments, (ii) ‘did not attend’ rates, and (iii) additional administrative activities. Data will also be collected from participants on (i) contact with general practitioner (GP), (ii) contact with hospital, (iii) use of additional couple support to estimate cost savings to the NHS. Modelling of this data will be applied to estimate likely volumes and patterns of demand, and staff burden, to estimate population-cost implications. Population costs will be estimated using epidemiological data on prevalence of men post-surgery for prostate cancer, alongside data on attrition from the intervention.

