## Background

Surgery is a major treatment modality for prostate cancer [1] and has been hypothesised to reduce mortality more than other treatments for localised prostate cancer [2]. However, the risks of surgery are known to include erectile dysfunction [3] even when nerve-sparing approaches are used [4]. Long-lasting sexual and urinary difficulties are the most common and troubling side-effects following radical prostatectomy [5] alongside loss of libido, ejaculatory dysfunction, orgasmic dysfunction and penile shortening [6]. Even at 24 months post-operatively, most men have not returned to their baseline measure of sexual function prior to surgery [7]. These side-effects can be distressing for men and their partners due to the impact on psychological well-being and couple intimacy [8-11].

Many men affected by prostate cancer and erectile dysfunction experience symptoms of anxiety and depression [12,13], with reduced quality of life directly associated with urinary and sexual body-image changes that occur after surgery [14]. Partners of these men also experience considerable psychological distress [9,15-17], with anxiety and depression often reported at higher levels for partners than for patients [18,19]. The difficulties experienced after surgery can also impact on the couple relationship itself; for instance, erectile dysfunction is associated with reduced wellbeing [20,21] and lower levels of dyadic adjustment in the first year after surgery [22].

Prostate cancer has been described as a ‘relationship disease’ [23] and it has been established that couples affected by prostate cancer often have significant unmet psychosexual supportive care needs around sexual recovery and rehabilitation [24,25]. With such evidence of the impact of sexual dysfunction on relationships, there has been increasing interest in the development of couple-based psychosocial interventions that aim to improve wellbeing and relationship quality. Couple-based interventions have been effective in reducing psychological distress [26] and facilitating healthy communication [27,28]. Sexual rehabilitation therapy has been particularly helpful in increasing use of erectile dysfunction medications [29] and re-establishing a sexual relationship [30,31].

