#### Outcome measures

The primary outcome measure (see below) assesses sexual functioning as part of a broader health-related quality-of-life measure. The secondary measures reflect the evidence that men and their partners require psychological (anxiety, depression), relational and sexual components to an intervention to meet the needs of this group.

Primary outcome measure

● Sexual functioning - EPIC measures general and sex-specific items related to prostate cancer [46]. EPIC is a comprehensive instrument that evaluates patient function and ‘bother’ after prostate cancer treatment. Potency of ≤60 in the sexual function domain is a clinical cut-off [42].

Secondary outcome measures

● Anxiety and depression - Hospital Anxiety and Depression score (HADS) measures psychological impact [61].

● Functional couple relationship - systemic core outcome measure (SCORE 15) measures relationship changes [62].

● Use of health services and erectile dysfunction medication/technologies, collated via a self-report questionnaire designed by the investigators.

Outcome measures will be assessed at baseline, at end of intervention and six months later.

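### The participant items for the economic analysis are framed only as NHS savings and leave out the erectile-dysfunction treatment use that the trial already collects

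*Protocol article*

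**What the plan says.** The section on long-term cost implications sets a two-sided scope: "Economic analysis will focus on additional costs, compared to usual care, and potential cost savings". The provider supplies cost inputs. The first is introduced by "Data will be collected from the organisation providing the intervention to provide estimates on (i) duration of appointments", followed by non-attendance rates and "iii) additional administrative activities". Participants supply a second list, with its purpose attached: "i) contact with general practitioner (GP), (ii) contact with hospital, (iii) use of additional couple support to estimate cost savings to the NHS".

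Under Outcome measures, one secondary outcome covers both health-service contacts and erectile-dysfunction treatment: "Use of health services and erectile dysfunction medication/technologies, collated via a self-report questionnaire designed by the investigators". The Background says of earlier work: "Sexual rehabilitation therapy has been particularly helpful in increasing use of erectile dysfunction medications". Objective 4 is to establish the long-term cost implications that a definitive trial would have to address.

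**The concern.** Two features of the participant list do not fit the rest of the article. First, the secondary outcome has two halves on one self-report form, health services and erectile-dysfunction treatment, and only the first half is carried into the economic list. The half left out is the one that the article's own Background gives a reason to expect might rise. Second, the listed items are tied to savings alone, although contacts with the GP, the hospital or further couple support could increase as well as decrease in the intervention arm.

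At stake is the incremental cost per couple against usual care, which feeds the affordability modelling. The pilot is meant to inform a definitive trial, so its list of resource items may be carried forward into that trial.

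**Working it through.** The article gives no unit cost, cost total or affordability figure, so there is no economic figure to reproduce. The check compares the sections and then looks at the sign of the omitted term.

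**Step 1: items collected against items costed.**

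| Item | Collected from participants (Outcome measures) | Named in the economic list |
|---|---|---|
| GP and hospital contact | Yes, as use of health services | Yes |
| Additional couple support | Not named separately | Yes |
| Erectile-dysfunction medication and technologies | Yes, named | No |

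The Statistical analysis section names only SCORE 15 and HADS as secondary outcomes for the between-group comparison, so that section does not take up treatment use either.

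**Step 2: is a change in the omitted item plausible?** The Background reports an increase with sexual rehabilitation therapy. The intervention borrows techniques from sex therapy, and its fourth session includes discussion of medical treatments. A rise is therefore plausible. It is not predicted: the expectations in the Statistical analysis section concern EPIC, SCORE 15 and HADS only.

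**Step 3: what the omission does.** Per couple, intervention minus control, let D be the delivery cost, S the net saving on the three listed items, and E the difference in the cost of erectile-dysfunction treatment.

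- Items as listed: D − S
- With the omitted item: D − S + E
- Error from the omission: −E. Cost is understated if E > 0 and overstated if E < 0.

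**Step 4: sign illustration.** All values are assumptions, with D set to 1 and E between −0.2 and +0.2. None comes from the article.

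| S | As listed, D − S | With E = −0.2 | With E = +0.2 |
|---|---|---|---|
| 0.1 | 0.9 | 0.7 | 1.1 |
| 0.5 | 0.5 | 0.3 | 0.7 |
| 0.9 | 0.1 | −0.1 | 0.3 |

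The table shows only that the omitted term can move the result either way and matters most when the net cost is near zero. It says nothing about the likely size.

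**Step 5: the savings framing.** S can be negative if contacts rise. A tabulation meant only to estimate savings has no natural place for that outcome, whereas a between-arm difference in cost does. The opening sentence of the section already promises a comparison of this two-sided kind, so the wording of the participant list is narrower than the section's own aim.

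**The case against.** The strongest reply is that this is one paragraph on simple modelling in a condensed article on a pilot. Nothing says that the list is exhaustive, and the erectile-dysfunction data are collected anyway, so they can still be costed at analysis and nothing is lost. Much of that stands, and it is why the point is modest. It does not remove it: the article sets out a numbered list that takes one half of a single outcome item and leaves the other, and a reader cannot assume that the missing half is included.

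A reader might infer more than the text supports, in four ways:

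- **That the whole economic section looks only for savings.** It does not. It opens with additional costs, and the provider items are costs. The savings wording belongs to the participant list alone.
- **That the population estimate ignores uptake.** The final sentence of the section, "Population costs will be estimated using epidemiological data on prevalence of men post-surgery for prostate cancer, alongside data on attrition from the intervention", does not name uptake, but the sentence before it says that the volume and pattern of demand will be modelled. Recruitment and ineligibility are also logged. The trial's recruitment figures are not a measure of service uptake, so they cannot show by how much the estimate would be wrong.
- **That leaving out training is an error.** Training is described under Phase 1 ("Specialist training in delivery of the intervention will be provided to practitioners holding accredited counselling or psychotherapy qualifications") and not named as a cost. Whether it is costed or treated as set-up depends on the costing perspective, a detail that a condensed article may leave to the full plan.
- **That the affordability result is bound to be biased.** With no costs given and the sign of E unknown, neither a size nor a net direction follows.

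**Conclusion.** The point holds in a limited form. The participant items named for the economic analysis omit erectile-dysfunction medication and technology use, although the trial collects it and the Background reports that a related therapy increased medication use. The named items are also described only as a source of NHS savings. If treatment use rises in the intervention arm, the incremental cost against usual care is understated by the cost of that rise.

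No monetary or relative size can be stated. The conclusion assumes that the participant list is followed as written and that the cost of this treatment falls within the perspective of the analysis, which the article does not settle for this item.

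**What to change.** In the section on long-term cost implications:

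1. Add erectile-dysfunction medication and technology use, as collected on the self-report questionnaire, to the costed participant items.
2. Replace the savings-only purpose with a between-arm difference in the cost of all participant resource use, which may be positive or negative. Combine it with the provider costs and report net incremental cost per couple.

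This takes a sentence or two of text and a little extra work to attach unit costs to the added item. No new data collection is needed, provided that the questionnaire, which is not shown, records enough about type and amount of use to be costed; that should be confirmed when the text is changed.
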